## Background

Cancer affects large groups of young adults, commonly defined as those between 18 to 39 years of age. Globally about one million young adults are diagnosed with cancer yearly, and the corresponding figure in Sweden is approximately 2000 [1, 2]. In addition to being a life-threatening condition, cancer and its treatments may impair several aspects of the general health, including sexual and reproductive functions. Being diagnosed with cancer during young adulthood can thus be particularly distressing by interfering with important life goals, such as establishing intimate relationships and building a family [3].

Previous research has reported that over 40% of young adults with cancer experience sexual problems within the first 2 years following diagnosis [4, 5]. Problems commonly reported by women include reduced sexual desire, vaginal dryness and/or dyspareunia, difficulties in sexual arousal and/or orgasm, and low satisfaction with sex life [6–8]. In men diagnosed with cancer erectile dysfunction, orgasmic difficulties, reduced sexual interest, and low satisfaction with sex life have been reported [9–12]. Sexual problems can be caused by several of the cancers common in the age group and their treatments (i.e., radiation therapy, chemotherapy, endocrine treatment, and surgery), directly or indirectly via physiological, psychological, and interpersonal factors [13, 14]. However, firm knowledge about the mechanisms involved in sexual problems after cancer in young adulthood is not yet established. Previous research has indicated that female gender, higher age, a poor prognosis, and being in a partner relationship predict more sexual problems [4].

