#### Cancer group – survey

##### Background variables

Background variables collected in the survey will include sociodemographic information on country of birth, educational level, occupation, partner relationship, children, and sexual orientation. Information on current cancer treatment and the use of fertility preservation procedures will also be included.

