### Statistical methods

The study will be reported following the STROBE statement [42] and the SPIRIT-PRO Extension [43]. Descriptive statistics will be used to determine the prevalence of sexual dysfunction and fertility-related distress by diagnosis and sex. These will be presented as means and standard deviations and as percentages of participants above the described cut-offs for these outcomes. Prevalence rates in the cancer group will be compared to prevalence rates in the general population by sex and age group, using Students’ t-test and χ^2^ tests. To determine predictors for sexual dysfunction and fertility-related distress at each assessment we will perform logistic regression models for each primary outcome (SexFS v2-domains and RCAC-dimensions) for the whole group and by sex. Independent variables will include sex (whole group), partner status, parenthood status, child wish (only for RCAC), satisfaction with sex life pre-diagnosis (only for SexFS v2), diagnosis, treatment intensity, body image, anxiety, and depression. Trajectories of these issues over time (T1, T2 and T3) will be analyzed with linear mixed models. Relations between sexual dysfunction and fertility-related distress, and between these issues and our secondary outcomes, will be analyzed with Pearson’s correlation coefficients. Statistical analyses will be performed in collaboration with external statisticians.

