## Discussion

This population-based cohort study aims to determine the prevalence and predictors of sexual dysfunction and fertility-related distress in young adults diagnosed with cancer. The results of the study will increase understanding of the trajectories of sexual dysfunction and fertility-related distress over 5 years following diagnosis.

Our study design includes a large nationwide sample of young adults diagnosed with different cancers and will therefore establish prevalence rates of sexual dysfunction and fertility-related distress over the first 5 years after diagnosis. One of the selected diagnoses, brain tumors, is a cancer often excluded in this kind of research and the group’s sexual dysfunction and fertility-related distress is still largely unknown. Potential participants will be identified through National Quality Registers with excellent coverage, ensuring that all individuals in the age group diagnosed with the selected cancers will be approached [44]. The design also allows for analyses of non-responders and attrition including highly reliable clinical variables. At the baseline assessment some patients may still be on treatment (e.g. lymphoma and breast cancers) and others will have finished their treatment (e.g. testicular cancer). Therefore, treatment status will be described in detail for each diagnosis when reporting prevalence at baseline, and all models will control for current treatment status. While most of the selected patient-reported outcome measures are standardized instruments, it should be noted that the study-specific measures, as well as the shortened versions of the BIS and RCAC for the comparison group, have not been validated. With a young adult comparison group assessed with the same standardized measures it will be possible to determine to what extent the self-rated problems are related to being treated for cancer. As the prevalence of sexual dysfunction in women and men has been reported to vary between countries [45, 46], the use of a comparison group randomized from the total general population in the country is a strength. However, the fact that the comparison group is only assessed at one time point is a limitation as it does not allow comparison of trajectories of these issues over time.

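### The covariate list for the predictor models leaves out age, which the protocol cites as a predictor of sexual problems, and current treatment status, which its Discussion says every model will control for

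*Protocol article*

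**What the plan says.** Under Statistical methods, predictors are to be found with logistic regression for each SexFS domain and each RCAC dimension, at each assessment, for the whole group and by sex. The covariates are given in one sentence: "Independent variables will include sex (whole group), partner status, parenthood status, child wish (only for RCAC"), then "satisfaction with sex life pre-diagnosis (only for SexFS v2), diagnosis, treatment intensity, body image, anxiety, and depression". Neither age nor current treatment status appears. Age enters the analysis section only as a stratifier in a different analysis: "Prevalence rates in the cancer group will be compared to prevalence rates in the general population by sex and age group".

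Two other places bear on that list.

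- The Background reports that "female gender, higher age, a poor prognosis, and being in a partner relationship predict more sexual problems".
- The Discussion notes that "At the baseline assessment some patients may still be on treatment (e.g. lymphoma and breast cancers"), while other groups will have finished, and concludes that "all models will control for current treatment status".

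The Background variables section shows that treatment status will be available from the survey: "Information on current cancer treatment and the use of fertility preservation procedures will also be included".

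**The concern.** Determining predictors is part of the primary objective, so the covariate list decides what the study reports.

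The two gaps differ in kind. For treatment status, the protocol contradicts itself. An analyst who follows Statistical methods fits models without the term, and one who follows the Discussion fits models with it. Treatment intensity does not fill the gap: it describes what treatment was given, not whether the patient is on treatment when answering the survey. The Discussion itself says that on-treatment status differs by diagnosis at baseline, and diagnosis is a listed predictor. Without the status term, a diagnosis odds ratio may partly reflect who is still being treated.

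For age, a predictor that the protocol cites is not carried into the models. Sex and partner status, from the same Background sentence, are. Across ages 18 to 39, parenthood and partner status can reasonably be expected to vary with age, and so can the mix of diagnoses. Their odds ratios may then carry part of an age effect.

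**Working it through.** **1. Count the listed covariates.** Each model uses either child wish (RCAC) or pre-diagnosis satisfaction (SexFS), not both.

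- Whole group: sex, partner status, parenthood, child wish or pre-diagnosis satisfaction, diagnosis, treatment intensity, body image, anxiety, depression = 9.
- By sex: the same without sex = 8.

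**2. Reproduce the plan's own figures (Sample size).**

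- Event rule: 5 events × 10 variables = 50 events, as stated.
- Sample chain: 1500 × 0.70 = 1050; 1050 × 0.80 = 840; 840 × 0.50 = 420; 1050 − 420 = 630. With 15% attrition, 630 × 0.85 = 535.5 (stated 535) and 535 × 0.85 = 454.75 (stated 454). These agree up to rounding.

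**3. Expected events.** Events = N × sex share × event rate, with the protocol's 35% men and 65% women, and its baseline event rates of 30% (men) and 60% (women), applied at every assessment.

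| Assessment | N | Men | Women | Whole group |
|---|---|---|---|---|
| 1.5 years (T1) | 1050 | 0.35 × 1050 × 0.30 = 110.3 | 0.65 × 1050 × 0.60 = 409.5 | 519.8 |
| 3 years (T2) | 535 | 0.35 × 535 × 0.30 = 56.2 | 0.65 × 535 × 0.60 = 208.7 | 264.8 |
| 5 years (T3) | 454 | 0.35 × 454 × 0.30 = 47.7 | 0.65 × 454 × 0.60 = 177.1 | 224.7 |

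**4. Events needed, as listed and with the two added terms.**

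| Model | Listed variables | Events needed | With age and treatment status | Events needed |
|---|---|---|---|---|
| Whole group | 9 | 45 | 11 | 55 |
| By sex | 8 | 40 | 10 | 50 |

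The whole-group model has at least 224.7 expected events against 55. Women have at least 177.1 against 50. Men have 110.3 and 56.2 against 50 at T1 and T2. Men at T3 have 47.7 against 50, which is 2.3 short, or 47.7 / 10 = 4.8 events per variable.

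**5. Two sensitivity checks.**

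- *Diagnosis as indicator terms.* Assume six diagnosis groups overall, three in men (brain, lymphoma, testicular) and five in women. The augmented models then have 8 + 5 + 2 = 15, 7 + 2 + 2 = 11 and 7 + 4 + 2 = 13 parameters, needing 75, 55 and 65 events. Only men at T3 fall short; men at T2 pass narrowly (56.2 against 55).
- *Departure to the RCT.* The 420 who leave follow-up all meet the dysfunction or distress criteria, so the share meeting them falls from 80% to (840 − 420) / 630 = 67%. Assume the men's event rate falls in proportion, from 30% to 25%. Men would then have 0.35 × 535 × 0.25 = 46.8 events at T2 and 0.35 × 454 × 0.25 = 39.7 at T3. Both are below 50, and the T3 figure is also just below the 40 needed for the list as it stands.

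**6. What cannot be computed.** The bias from omitting age depends on the age effect and on the age difference between categories given the other covariates. The documents give neither. They also give no proportion on treatment by diagnosis.

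**The case against.** The strongest reply is that treatment status is planned. The Discussion commits to it, the survey collects it, and the covariate sentence is not worded as a closed list. The Setting section also expects most participants to have completed first-line treatment by baseline. Part of this stands: the defect is a contradiction to be reconciled, not proof that the term would be left out. A reader might infer that diagnosis effects are confounded by treatment status; that holds only if the Discussion is ignored. The open-list reading is weak, however, because the sentence assigns covariates by outcome and model, and Sample size caps their number.

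On age, four limits stand.

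- The Background sentence concerns sexual problems and says nothing about fertility-related distress.
- The aim is prediction. A coefficient not conditioned on age is a different association, not automatically a biased one. That does not explain leaving a cited predictor out of a search for predictors.
- Age is in neither the survey's background list nor the registry list. Its availability is a fair inference from the eligibility criteria and the age-group comparison.
- A fuller analysis plan may settle the covariates. That could cure the age gap, but the published article would still contradict itself on treatment status.

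A reader might also try to size the age bias. An assumed odds ratio of 1.03 to 1.05 per year and an assumed 4 to 6 year age gap would multiply a category's odds ratio by 1.03^4 = 1.13 to 1.05^6 = 1.34. Neither input comes from the documents, and the formula uses an unadjusted gap where an adjusted one is needed. Nor does the direction follow from the Background sentence, because the documents do not say which categories are older.

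**Conclusion.** The point holds in a limited form. The covariate list omits a predictor that the protocol cites for sexual problems, and it conflicts with the protocol's own commitment on treatment status. The odds ratios for diagnosis, parenthood and partner status may carry age or on-treatment effects. The documents do not show that they do, or by how much, or in which direction. For RCAC, the argument for age is general reasoning only.

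The sample-size rule does not explain the omission. On the protocol's assumed sex split, event rates and attrition, both terms are affordable in every model except the men's 5-year model, which has about 48 expected events against 50. The follow-up margins for men also depend on the 30% event rate persisting after RCT participants leave.

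**What to change.** In Statistical methods, add age (one continuous term) and current treatment status at that assessment to the list for every predictor model, whole group and by sex, so that the section agrees with the Discussion. For RCAC, give the reason for including age, since the Background sentence does not cover it.

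Under Sample size, restate the event count: 11 variables and 55 events for the whole group, 10 variables and 50 events by sex. The ceiling of ten variables must be reworded, because the whole-group model exceeds it although its events are ample.

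The cost is a sentence and two terms per model, using information that the study collects or can be expected to hold. The downside to state is the small shortfall for men at 5 years (about 48 expected against 50). Further terms, such as a non-linear age term, would widen it to at least 55 needed.

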### Variables

The primary outcomes will be sexual function and fertility-related distress. Secondary outcomes will be body image, anxiety and depression, health-related quality of life, self-efficacy related to sexuality and fertility, and fertility-related knowledge. Primary and secondary variables will be collected in the survey. Before conducting the Fex-Can Cohort, the primary outcomes were tested in two pilot studies: one including young women diagnosed with breast cancer (*n* = 181) [7], and one including young men diagnosed with testicular cancer (*n* = 111) [11]. The results showed the instruments to be well accepted. All primary and secondary outcomes will be included in the survey at each assessment. Additionally, background variables (see below) will be collected via the survey at baseline and at follow-ups. Clinical variables (diagnosis, stage, treatment, relapse) will be extracted from registry data and updated in connection with each data collection. See Table 1 for overview of assessments.

**Table 1 Tab1:** Overview and timing of assessments in the Fex-Can Cohort

Type of data	Time of diagnosis / treatment start	Baseline 1.5 years	Follow-up 3 years	Follow-up 5 years
Mode of administration				
Survey data				
Background variables		X	X	X
Sexual function (SexFS v2)		X	X	X
Fertility-related distress (RCAC)		X	X	X
Anxiety and depression (HADS)		X	X	X
Health-related quality of life (EORTC QLQ-C30)		X	X	X
Body Image (BIS)		X	X	X
Self-efficacy		X	X	X
Fertility-related knowledge		X	X	X
Clinical data	X^a^	X^b^	X^b^	X^b^

^a^Extraction of data from respective quality registry at time of baseline-assessment

^b^Updated information extracted from the quality registries in connection to analyses

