##### Body image

Body image will be assessed with the Body Image Scale (BIS) that measures perception of one’s body image associated with cancer and cancer treatment [32]. The BIS comprises 10 items and responses are given on a four-point scale (ranging from 0 = Not at all to 3 = Very much) with higher scores indicating a more negative body image. Total summary scores can range between 0 and 30, and a total score exceeding 10 is suggested to reflect a negative body image reaching a clinical level [32, 33]. The BIS has shown high test-retest reliability and satisfactory internal consistency in cancer patients [32].

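### The predictor models put body image, anxiety and depression (same-survey secondary outcomes) beside diagnosis and treatment intensity, so those odds ratios can understate overall associations, and at T1 the three variables are concurrent correlates

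*Protocol article*

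**What the plan says.** All references are to the protocol article.

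- **Variables:** "Secondary outcomes will be body image, anxiety and depression, health-related quality of life", among others. On timing: "All primary and secondary outcomes will be included in the survey at each assessment". Body image (BIS), anxiety and depression (HADS) are therefore measured at the same moments, in the same questionnaire, as sexual function and fertility-related distress.
- **Statistical methods, models:** "To determine predictors for sexual dysfunction and fertility-related distress at each assessment we will perform logistic regression models for each primary outcome", for the whole group and by sex. The independent variables are sex (whole group), partner and parenthood status, child wish or pre-diagnosis sexual satisfaction, and then "diagnosis, treatment intensity, body image, anxiety, and depression". The Discussion adds current treatment status to all models.
- **Statistical methods, correlations:** the links "between these issues and our secondary outcomes, will be analyzed with Pearson’s correlation coefficients". The same variables are thus outcomes, correlates and predictors.
- **Background:** the cancers and their treatments can cause sexual problems "directly or indirectly via physiological, psychological, and interpersonal factors". It also reports that fertility-related distress is related to depressive symptoms in the long term, and that the threat of infertility is associated with a poorer body image.
- **Body image:** the BIS measures "body image associated with cancer and cancer treatment".

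**The concern.** Diagnosis and treatment intensity are fixed early and come from the registries. Body image, anxiety and depression are reported by the patient about 1.5 years or more after diagnosis, together with the outcome. Putting them all in one covariate list raises two problems.

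1. **Possible mediators.** If treatment worsens body image or mood, and these worsen sexual function or fertility distress, the adjusted treatment odds ratio counts only the part that bypasses them.
2. **Possible consequences.** If the sexual or fertility problem itself lowers mood or body image, the coefficient for depression or body image partly reflects the outcome acting on the covariate. Reporting it as a predictor would mislead.

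Predictors are part of the primary objective, and the Abstract gives identifying patients in need of support as the motive. A diagnosis or treatment group at high overall risk could look unremarkable because its distress scores have absorbed the association.

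**Working it through.** **Step 1. What the text fixes.** No figure in the protocol tests this point directly, so the first check is to set the sections side by side.
- Variables and Statistical methods together fix that the three scores are same-survey secondary outcomes and also independent variables beside diagnosis and treatment intensity.
- Background and Body image describe a route from cancer or treatment through psychological factors, and fertility distress as linked to later depressive symptoms.
- T1 is the first survey wave, so no earlier BIS or HADS score exists. At T1 the three variables can only be concurrent.
- For T2 and T3 the article does not say whether the scores come from T1 or from the same wave.

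**Step 2. Mechanism, under assumed effects (none of these values is in the protocol).**
- *One mediator, n = 400,000.* Treatment shifts the mediator by 0.6 SD. With mediator log-OR 0.6 and direct log-OR 0.36, the treatment OR is 1.95 without the mediator and 1.43 with it. With mediator log-OR 0.8 and direct log-OR 0.2, it is 1.82 and 1.22. The adjusted values are simply the direct effects that were put in: exp(0.36) = 1.43 and exp(0.2) = 1.22.
- *Three correlated mediators, n = 200,000.* Direct log-OR 0.4 (exp(0.4) = 1.49), shifts of 0.2 to 0.5 SD, log-OR 0.2 to 0.35 per SD for each mediator. The treatment OR is 1.63 to 2.23 without them and 1.47 to 1.51 with them.
- *Reverse direction.* If dysfunction raises depression by 0.5 SD and depression has no effect on dysfunction, the concurrent model still gives an OR of about 1.67 per SD for depression. This is close to exp(0.5) = 1.65, as expected.

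**Step 3. Room for a two-model approach.** The Sample size section's own figures reproduce:
- 1500 × 0.70 = 1050; 1050 × 0.80 = 840; 840 / 2 = 420; 1050 − 420 = 630.
- 630 × 0.85 = 535.5 (stated 535); 535 × 0.85 = 454.75 (stated 454).

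The tightest case is men at T3. With the protocol's 35% men and 30% event rate carried forward, 454 × 0.35 × 0.30 = 47.7 events. At 5 events per variable, 47.7 / 5 = 9.5 variables. Counting variables as the protocol does:

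| By-sex model | Variables | Events needed |
|---|---|---|
| Without BIS and HADS, with treatment status | 6 | 30 |
| With BIS, anxiety and depression | 9 | 45 |
| Also with the T1 outcome | 10 | 50 |
| Also with age | 11 | 55 |

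The first two fit within 47.7 events; the last two do not.

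**The case against.** Several counterarguments are strong.

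- **No causal estimand is stated.** The protocol looks for predictors and potential predictors, and never says that the treatment odds ratio is a total effect. A reader might infer that the planned models are biased. The documents do not support that: in the simulations each model recovers its own quantity, and the smaller odds ratios are the assumed direct effects. What remains is that the protocol reports only the quantity net of the distress scores, without saying so.
- **The follow-up models.** A reader might infer that the T2 and T3 models ignore the T1 scores. That would be reading silence as a decision. Modelling at each assessment may describe only the timing of the outcome, the covariate list is open, and T1 outcomes do enter the linear mixed models. Only the lack of a stated wave can be said.
- **Single-step entry.** The article fixes no order of entry, and a staged fit is compatible with it. A condensed article may leave that to a fuller plan. But the covariate list is printed here, and an open list can add variables without removing the three.
- **Psychological markers are legitimate candidates** for finding patients in need. This stands, and is why they are kept in a second model. At T1, however, a score from the same questionnaire does not forecast the outcome.
- **Adjusting follow-up models for the T1 outcome** may look like a natural remedy. For the treatment odds ratios it is not: most participants are expected to have completed first-line treatment by T1, so the T1 outcome is itself post-treatment, and adjusting for it would block the same pathway.

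**Conclusion.** The point holds as one of specification and labelling. With body image, anxiety and depression in the model, the diagnosis and treatment odds ratios can understate the overall associations, and the T1 coefficients of the three scores are concurrent associations that may run in either direction.

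The size is unknown. Attenuation follows if treatment worsens these scores and the scores worsen the outcome. The protocol's Background makes this plausible but gives no effect sizes, and other patterns could shift the odds ratios differently. The simulated ranges illustrate the mechanism and are not estimates for this cohort. The event counts assume that the baseline event rate and sex split carry forward to T3.

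The study's data collection is unaffected, but part of the primary objective is, so the change is worth making before analysis.

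**What to change.** For each outcome, report two models.

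1. **First model:** the listed sociodemographic and pre-diagnosis variables, diagnosis, treatment intensity and current treatment status, without BIS and HADS. Take the diagnosis and treatment odds ratios from this model at every wave, and do not adjust it for the T1 outcome.
2. **Second model:** add BIS, anxiety and depression. At T1, label their coefficients concurrent associations. At T2 and T3, state that the T1 scores are used, so that they precede the outcome.

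Adjustment for the T1 outcome belongs at most in a secondary prognostic model where events allow. For men at T3, with about 48 events (about 9 variables), adding it to the full list would exceed the protocol's own rule.

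**Cost:** no new data, and the first model has three fewer variables than the planned one. The burden is one additional model per outcome, sex group and wave. There are 14 outcomes for women (8 SexFS domains and 6 RCAC dimensions), 11 for men (5 and 6) and 10 common to both sexes (4 and 6). That is 14 + 11 + 10 = 35 additional models per wave, or 35 × 3 = 105 in all if every combination is fitted.
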